### ***Randomization***

Treatment allocation of real abdominal acupuncture or sham abdominal acupuncture for each eligible patient in the study will be determined by a randomization process. The random allocation to the 2 arms of the study will be performed using a computer software named Random Allocation Software [23], following a balanced 1:1 pattern (real abdominal acupuncture:sham abdominal acupuncture) based on a block design where the block size is not constant. This will be carried out by an administration staff of the centre who is not involved in the study and the information of the allocation list will remain strictly confidential. All participants, screeners, practitioners and outcome assessors involving in this study are masked to the whole randomization process. Random assignments cannot be viewed in advance nor changed after randomization. The specific treatments patients are assigned to are only revealed to the practitioners immediately prior to treatment.

### ***Background of practitioners***

The treatments of the study will be performed by RCMPs who have over 3 years experience in acupuncture and possess specialty in administering abdominal acupuncture. The RCMPs in this study should strictly adhere to the study protocol and trained to be familiar with administering study treatments. Besides, they should have full understanding of the procedure to carry out sham abdominal acupuncture. Furthermore, they should agree to accept the allocation of treatment and would not deviate, treat each patient to the best of their professional skills and attention for all study subjects. The practitioners will be asked to maintain the same attitude to both treatment groups to avoid any psychological influences.

### ***Treatment details***

The abdominal acupuncture, a therapeutic microsystem based on traditional Chinese medicine acupuncture meridian theory and new concepts developed by [name] Bo [11-14], will be used for acupuncture point selection and administration in this study. Patients will undergo a total of 6 treatments as previous articles or reviews have shown that six or more acupuncture treatments were significantly associated with positive outcomes [24-25]. Both real and sham abdominal acupuncture groups will be treated every other day, three times a week for 2 weeks (6 treatments in total). The treatments will be provided at no cost to all participants. Electrostimulation, moxibustion, cupping, tuina, and any other non-needle treatments and adjuncts will not be allowed in this study. Any adverse reactions or collateral effects will be recorded with detailed explanation of their type and the dates on which they occurred.

### ***Real abdominal acupuncture treatment***

In the real treatment group, a pre-defined standardized abdominal acupuncture prescription that has been used in previous studies for neck pain will be employed [11, 15,17]. The acupuncture points used will be: Zhongwan (CV12), Guanyuan (CV4), bilateral Shangqu (KI17) and bilateral Huaroumen (ST24) and they are shown in Figure 2. Abdominal acupuncture treatments will be provided using sterile, single-use, disposable Bo's abdominal acupuncture needles (40 mm x 0.22 mm) (Changzi City Enyi Science and Technology Co., Ltd, China) with the aid of guide tubes for inserting needles. The patient wearing eye mask will be lying in a supine position and the abdomen is exposed. The abdomen is examined for any contraindication to abdominal acupuncture and the skin will be sterilized before needle insertion. Then, the location of the Conception Vessel is defined. Each treatment begins with needle insertion in the acupuncture points Zhongwan (CV12) and Guanyuan (CV4) for

invigorating the spleen and tonifying the kidney of the body, followed by the rest of the acupuncture points. The abdominal acupuncture treatment will include three steps, namely, awaiting qi, move qi and hastening qi. The first step is awaiting qi. It works by means of inserting the needles perpendicularly with the use of guide tubes to superficial level of skin for all the selected acupuncture points. After 3 to 5 minutes, it will progress to the step of move qi. This will be done by inserting the needles perpendicularly in the acupuncture points Zhongwan (CV12) and Guanyuan (CV4) deeply down to superficial level of the abdominal muscle (deep needling, to a depth of 20–35 mm), bilateral Shangqu (KI17) to the superficial layer of abdomen (shallow needling, to a depth of 5 mm) and inserting the needles for bilateral Huaroumen (ST24) down to subcutaneous abdominal fat (medium needling, to a depth of 10–20 mm). Then, it is followed by hastening qi by making appropriate adjustment on the depth of the needles according to pain relief condition of patients. The manipulation method is light and only minimal twirling is required. Responses such as obtaining qi or muscle twitch responses will not be sought. The needles will be retained for 30 minutes with an infrared therapeutic lamp (Chongqing Xinfeng Medical Instruments Co., Ltd, China) being placed 30 cm directly over the navel. After finishing the needles retention time, the needles will be removed following the sequence of acupuncture point insertion. Each insertion hole will be pressed for a while with a dry sterilized cotton ball immediately after withdrawal of the needle following the open-closed supplementation and draining method.

Figure 2. The acupuncture points used in the study

[figure not shown]

### *Sham abdominal acupuncture treatment*

In the sham treatment group, single-use, disposable non-penetrating blunt sham needles with guide tubes will be used. The acupuncture points used will be 1 *cun* away from the points used in the real abdominal acupuncture group. After the skin sterilization, the RCMP will mimicked the real abdominal acupuncture treatment by using the blunt sham needle with the patient lying in a supine position and wearing eye mask. The RCMP will pretend to insert needle using guide tubes similar to real abdominal acupuncture treatment. When the needle is pressed on the skin, the blunted tip will touch the skin, giving patient feeling of real needle insertion. The treatment procedure and techniques used in this group will be the same as the real treatment group. An infrared therapeutic lamp (Chongqing Xinfeng Medical Instruments Co., Ltd, China) will be placed 30 cm directly over the navel for the duration of the

30-minute retention time in each treatment session.

After the completion of the 4-week follow-up, the patients randomized to this group will receive compensation treatments of real abdominal acupuncture as described in the real treatment group.

Throughout all the treatment sessions for both real and sham abdominal acupuncture groups, a screen and eye masks will be used to obstruct patients' sight from seeing the needles.

### ***Co-interventions***

During the study period which includes the follow-up period of the study, each participant is advised by the practitioner to avoid other treatments such as physiotherapy, acupressure, cupping, tuina, reflexotherapy, chiropractic or bone-setting for neck pain. This will be reinforced by the research assistant during the entry period and at each evaluation time point. In the event that a patient has attended other co-interventions for neck pain, including using pain relief medications, it should be reported to the research assistant during each evaluation period and the information will be recorded by the research assistant. However, general light exercises are allowed for all patients participating in the study.

### ***Ethical considerations***

This study will adhere to the common guidelines of the Declaration of Helsinki for medical research involving human subjects [26-27] and the International Conference on Harmonisation – Good Clinical Practice Guidelines [28]. Prior ethical approval will be obtained from the Joint CUHK–NTEC Clinical Research Ethics Review

Committee before the commencement of the study. Prior verbal and written consent will be obtained from each patient participating in the study.

### ***Stopping rules***

The study will be stopped if the principal investigator believes that there is an unacceptable risk of serious adverse event in one or more of the treatment groups.

### ***Outcome measurements***

#### ***Baseline information***

Sociodemographic information of all participants, including age, gender, education background and neck pain history including pain sites (unilateral neck, bilateral neck, central neck), pain duration, pain occurrence, previous neck injury, and previous neck treatments, will be recorded at baseline interview. An outcome assessor who is masked to treatment allocation will conduct assessments.

The study's primary endpoint will be immediately after the intervention ends. Table 1 below summarizes the categories of information and measurements that are included in the baseline and follow-up interviews.

Table 1. Content of baseline and follow-up assessments

| Measures                                   | Baseline | Finished | 4-week | 12-week |
|--------------------------------------------|----------|----------|--------|---------|
| Inclusion and exclusion variables          | X        |          |        |         |
| Sociodemographic characteristics           | X        |          |        |         |
| Neck pain history                          | X        |          |        |         |
| Neck Pain Questionnaire - Real             | X        | X        | X      | X       |
| - Sham                                     | X        | X        | X      |         |
| VAS for pain intensity † - Real | X        | X        | X      | X       |
| - Sham                                     | X        | X        | X      |         |
| SF-36v2 Health Survey - Real               | X        | X        | X      | X       |
| - Sham                                     | X        | X        | X      |         |
| Credibility test                           | X        | X        |        |         |
| Satisfaction with treatment                |          | X        |        |         |
| Blinding assessment †           |          | X        |        |         |
| Use of medications *            | X        | X        | X      | X       |
| Adverse experiences *           |          | X        | X      | X       |
| Dropouts and withdrawals *      | X        | X        | X      | X       |

\* At every single visit; † After the first treatment

### *Primary outcome measure*

The primary outcome measure is the Northwick Park Neck Pain Questionnaire (NPQ) [29]. It is a questionnaire used to evaluate functional performance in patients with neck pain [5]. In this study, the validated Chinese version of the NPQ will be used [30-32]. It consists of nine five-part questions to assess the patient's symptoms and a score is obtained [29]. The questions cover activities which are likely to be affected

by neck pain. Each question contains five statements of increasing difficulty and is scored between 0 to 4. The NPQ will be scored out of 36, or 32 for non-car drivers, and is presented as a percentage [29,33]. In this study, the questionnaire will be assessed at baseline, immediately after the intervention ends, at 4-week, and 12-week follow-up interviews for real abdominal acupuncture group. As for sham abdominal acupuncture group, the questionnaire will be assessed at baseline, immediately after the intervention ends, and at 4-week follow-up interview.

### *Secondary outcome measures*

The visual analogue scale (VAS) for pain is a measurement of pain intensity and has widely used [5,34]. This is a continuous scale of 10-cm in length. Participants will be asked to mark on the scale 0 (no pain) to 10 (worst imaginable pain), the degree of intensity of neck pain experienced on the day the assessment is performed. This item will be assessed at baseline, after the first treatment, immediately after the intervention ends, at 4-week, and 12-week follow-up interviews for real abdominal acupuncture group. As for sham abdominal acupuncture group, it will be assessed at baseline, after the first treatment, immediately after the intervention ends, and at 4-week follow-up interview.

The SF-36 Health Survey is a generic questionnaire that used to measure the general health status, including physical and mental components, with higher scores indicate better health [5,35]. In this study, the validated Chinese (HK) SF-36v2 Health Survey will be used [36]. This measure will be assessed at baseline, immediately after the intervention ends, at 4-week, and 12-week follow-up interviews for real abdominal acupuncture group. As for sham abdominal acupuncture group, it will be assessed at baseline, immediately after the intervention ends, and at 4-week follow-up interview.

### *Other measures*

The well-validated credibility scale developed by Borkovec and Nau [37] which has previously been used for acupuncture studies, will be used to ascertain treatment credibility in the two groups [35,38-39]. All participants will be asked, “How confident do you feel that this treatment can alleviate your complaint?”, “How confident would you be in recommending this treatment to a friend who suffered from similar complaints?”, “How logical does this treatment seem to you?” and “How successful do you think this treatment would be in alleviating other complaints?” at baseline and immediately after the intervention ends, scoring on a 0 to 6 Likert scale, with 6 indicating higher credibility [35].

A global measure of satisfaction with care and treatment outcome will also be evaluated immediately after the intervention ends (the end of 6 treatments). All patients will need to answer the question: “All things considered, how satisfied are you with the results of your recent treatment for neck pain?” (1 = extremely satisfied, 2 = very satisfied, 3 = somewhat satisfied, 4 = mixed (approximately equal satisfaction and dissatisfaction), 5 = somewhat dissatisfied, 6 = very dissatisfied, 7 = extremely dissatisfied, 8 = not sure/no opinion) [40].

Blinding assessments will be evaluated after the first treatment and immediately after the intervention ends to test blinding to the two treatment groups. Patients in both real and sham abdominal acupuncture groups will be asked to guess whether they are in the real treatment group or the sham control group. Besides, in order to examine the efficacy of the blinding technique of this study, the subjects will be asked to select an answer for the question “How did you feel when the acupuncture needle was inserted?”

The available answers are: (1) needles were inserted into the muscle; (2) needles did not penetrate the skin; and (3) I could not discriminate the difference [41].

Patients' use of pain relief medications during the study period will be recorded throughout the study period.

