## **Methods**

### ***Study design***

This study is a single center, patient and assessor-blind, placebo-controlled, parallel-group study with balanced randomization that compares standardized abdominal acupuncture with controlled non-penetrating sham abdominal acupuncture. The trial will be conducted at Pok Oi Hospital – The Chinese University of Hong Kong Chinese Medicine Centre for Teaching and Research (Shatin). Clinical ethics approval will be obtained from the Joint CUHK–NTEC Clinical Research Ethics Review Committee before the trial starts. Eligible participants are blinded to treatment group allocation. The participants will be told before randomization that they are allocated to one of two groups. They will be informed that the treatment might or might not prove to be effective and that there will be a 50% chance of assigning to a sham group but do not tell what the sham treatment is. The outcome assessment and statistical analysis will be performed by a research assistant who is also blinded to patient assignment.

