### ***Recruitment***

Participants will be recruited through advertisements or posters posted on bulletin boards of all Chinese medicine centers, polyclinics and mobile clinics under Pok Oi Hospital and leaflets delivered through these sites. Patients interested in participating in the study will be referred to Pok Oi Hospital – The Chinese University of Hong Kong Chinese Medicine Centre for Teaching and Research (Shatin) to undergo a process to determine eligibility. They will be first screened and checked by Hong Kong Registered Chinese Medicine Practitioners (RCMPs) who have at least 3 years clinical experience and have received pre-study training by a senior RCMP. The RCMPs will run down the checklist of inclusion and exclusion criteria. A full medical history will be obtained, as well as clinical examination and cervical radiography. The clinical examination consist of inspection of the neck and shoulder regions for muscle

atrophy and dislocations, active and passive movements of neck and shoulder joints and provocation tests of neck and shoulder muscles. Those suitable to be recruited to the study will be asked to see the research assistant of the center. Then, the research assistant will explain the overall objectives and nature of the study and guides them through the informed consent process. The research assistant will administer the baseline questionnaire and written informed consent. This is followed by random allocation to real abdominal acupuncture group or sham abdominal acupuncture group by an administration staff of the Chinese medicine center. After randomization, the research assistant will schedule treatment procedure. The study flow is shown in Figure 1.

Figure 1. The study flow of abdominal acupuncture for neck pain

[figure not shown]

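### Treatment credibility is rated only before allocation and after all six treatments, so no planned rating compares the arms once treatment has been experienced but before most of the response has accrued

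*Protocol*

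**What the plan says.** Under Other measures, the protocol states that the credibility scale "will be used to ascertain treatment credibility in the two groups". All participants answer four questions "at baseline and immediately after the intervention ends, scoring on a 0 to 6 Likert scale". Table 1 agrees: the credibility row is marked at Baseline and Finished. It lacks the dagger for an assessment after the first treatment, which appears on the rows for pain intensity (visual analogue scale, VAS) and blinding.

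The Recruitment section fixes the order of the baseline step: "The research assistant will administer the baseline questionnaire and written informed consent". The next sentence reads "This is followed by random allocation to real abdominal acupuncture group or sham abdominal acupuncture group". Under Study design, patients are told before randomisation that "there will be a 50% chance of assigning to a sham group but do not tell what the sham treatment is".

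The satisfaction paragraph of Other measures explains what the end-of-intervention time means: "immediately after the intervention ends (the end of 6 treatments". Treatment details gives the course as "three times a week for 2 weeks (6 treatments in total". Baseline information adds: "The study's primary endpoint will be immediately after the intervention ends".

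**The concern.** A credibility scale in a sham-controlled trial should show whether both arms found what they received equally believable, as far as possible independently of how well it worked. That calls for a rating made after patients have experienced their assigned procedure and before most of the outcome is known to them. The protocol schedules one rating before that window and one after it, and none inside it.

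What is at stake is the interpretation of a positive result. If the real arm does better on the NPQ and also scores higher on credibility at the end, one explanation is that a less convincing sham produced the difference in outcome. Another is that better outcomes produced the difference in credibility. The credibility data as scheduled cannot cleanly separate the two, and no later analysis can recover a rating that was never taken.

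**Working it through.** No figure in the protocol is in dispute. The check is on timing, followed by an illustration of size.

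**Timing**

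| Step | Patient's knowledge or experience | Credibility rated? |
|---|---|---|
| Baseline questionnaire, at consent (Recruitment) | Not allocated or treated; knows of a 50% chance of an undescribed sham (Study design) | Yes |
| Random allocation (Recruitment) | – | – |
| After first treatment (Table 1 dagger) | One session of the assigned procedure | No; VAS and blinding assessment only |
| After all six treatments (Other measures; Table 1) | Full course completed; time of the primary endpoint | Yes |

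**Baseline rating.** Both arms rate the same prospect. By randomisation the expected between-arm difference is 0, whether the sham is convincing or transparent. With 77 per arm, the standard error of a standardised difference is √(2/77) = 0.16 SD, and all of that variation is chance.

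**End rating.** The questions about relief of the patient's own complaint and about recommending the treatment to a friend invite an answer based on the patient's own result. The questions about how logical the treatment seems and about other complaints do so less. The rating is therefore partly, not wholly, driven by outcome.

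**Illustration of size.** The correlation and outcome difference below are assumptions; the protocol gives neither.
- Completers per arm: 77 × (1 − 0.15) = 65.45, taken as 65 (Sample size determination).
- The sham is equally credible in itself, and the arms differ in end-of-treatment credibility only through outcome.
- r is the within-arm correlation of credibility with outcome, 0.3 to 0.7. d is the true outcome difference, 0.2 to 0.5 SD.
- Induced credibility difference: r × d.
- Probability that the sham is declared less credible, two-sided 5% test, normal approximation, counting that direction only: Φ(r·d·√(65/2) − 1.96), with √(65/2) = 5.70.

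| d | r | r × d (SD) | Probability |
|---|---|---|---|
| 0.2 | 0.3 | 0.06 | 0.053 |
| 0.2 | 0.7 | 0.14 | 0.123 |
| 0.4 | 0.5 | 0.20 | 0.206 |
| 0.5 | 0.3 | 0.15 | 0.135 |
| 0.5 | 0.7 | 0.35 | 0.514 |

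For the last row: 0.35 × 5.70 = 1.995; 1.995 − 1.96 = 0.035; Φ(0.035) = 0.514. With no induced difference the probability in this direction would be 0.025. The distortion is slight at the low end and substantial at the high end.

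**The case against.** The strongest reply is that the protocol already checks the sham early. After the first treatment, patients guess their group and say whether they felt needles enter the muscle, felt no penetration, or could not tell. For a non-penetrating sham this is the most direct check on detection, and it comes before most of the outcome. This stands and reduces the harm considerably. It does not remove the point. A guess at allocation and a report of sensation are different constructs from confidence in a treatment and its perceived logic, and the protocol lists them as separate measures.

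The two scheduled ratings also have uses. The baseline rating records expectancy and allows a check for chance imbalance. Similar end-of-treatment scores in both arms would give some reassurance, and a difference could be read alongside the NPQ and VAS from the same visit. Both uses stand. A reader might infer that the end rating is completely confounded with response, or that neither rating is usable. The documents do not support that: two of the four questions do not ask about the patient's own result, and the illustration shows partial confounding that is small under its milder assumptions.

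Finally, a rating after session 1 would not be free of response. Under Real abdominal acupuncture treatment, needle depth is adjusted within the session according to pain relief, and VAS is repeated after the first treatment. The protocol thus anticipates some early response. This stands as a limit on the remedy: such a rating would probably be less contaminated than one after six sessions, but not clean.

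**Conclusion.** The point holds as one of measurement timing. The stated purpose is a comparison of credibility between the arms. One of the two planned ratings cannot inform that comparison, and the other informs it only in a form mixed with perceived benefit. On the assumptions above, an equally credible sham would be declared less credible about 5% to 51% of the time. That range rests on assumed correlations and effect sizes and shows scale only.

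A reader might go further and infer that the trial could not tell a non-credible sham from an effective treatment, or that its main result is undermined. Neither follows. The early blinding assessment supplies separate evidence on sham detection. Credibility is listed under Other measures, as neither a primary nor a secondary outcome, and Statistical methods and analysis specifies no credibility adjustment of the NPQ. The primary NPQ analysis is unaffected. The weakness is in the supporting evidence on sham adequacy, and correcting it is a cheap improvement, not the repair of an error in the analysis.

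**What to change.** - Add the four credibility questions at the contact after the first treatment, where VAS and the blinding assessment are already collected.
- Name that score in Other measures as the main between-arm comparison of credibility.
- Keep the baseline rating as a measure of expectancy and the end-of-treatment rating as supportive.
- Add the dagger to the credibility row of Table 1.

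The cost is a few minutes at session 1. No new visit is needed and the treatment does not change. Some within-session response may still influence the rating; the VAS taken at the same contact allows that to be examined.

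### The needle-sensation item, on its natural reading asked after session 1 as well as at the end, may cue patients to what the sham is before five further sessions and the patient-reported outcomes

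*Protocol*

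**What the plan says.** Four parts of the protocol bear on this.

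- **Study design.** Before randomization, patients are told of "a 50% chance of assigning to a sham group but do not tell what the sham treatment is".
- **Sham abdominal acupuncture treatment.** In the control arm "single-use, disposable non-penetrating blunt sham needles with guide tubes will be used". An eye mask and a screen hide the needles during sessions.
- **Other measures.** "Blinding assessments will be evaluated after the first treatment and immediately after the intervention ends". Patients in both arms guess real or sham. The same paragraph adds a question on how insertion felt, with three permitted answers: insertion into the muscle, "2) needles did not penetrate the skin; and (3) I could not discriminate the difference".
- **Baseline information, Table 1.** The blinding row is marked for the end of treatment and carries a dagger, which the footnote explains as "After the first treatment".

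There are six sessions (Treatment details). The primary endpoint is the NPQ immediately after the last of them (Baseline information; Primary outcome measure).

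**The concern.** The patient blind rests on two things: patients cannot see the needles, and they do not know what a sham would be. The sensation item weakens the second. A patient who knows that half of participants receive sham, and who is asked in one sitting to guess the arm and to say whether the needles failed to penetrate, needs one step to infer what the sham is.

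Sessions 2 to 6 could then be experienced with that in mind. The mask and screen work only during sessions. In the real arm the protocol itself expects a mark: "Each insertion hole will be pressed for a while with a dry sterilized cotton ball".

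NPQ, VAS and SF-36v2 are all answered by the patient, so a blinded assessor does not protect them if the patient's belief about allocation changes. The end-of-treatment guess would also be harder to interpret, because it could not separate a sham that failed from a cue supplied by the questionnaire.

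**Working it through.** The check is mainly a reading of the protocol. No figure in it is wrong on this point.

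**1. Is the option the sham's defining feature?** Yes. Study design says the trial "compares standardized abdominal acupuncture with controlled non-penetrating sham abdominal acupuncture", and the sham section specifies blunt needles that do not enter the skin. The second answer option describes that same property.

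**2. When is the item asked?** The blinding paragraph gives two times, then describes the guess, then adds the sensation question for the same purpose with no time of its own. The Table 1 dagger covers the whole row. Both times therefore apply to both items on the natural reading. This is an inference; nothing states it separately for the sensation item, and nothing limits the item to the end.

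**3. What follows the first asking?** Sessions remaining: 6 − 1 = 5. After them come the primary NPQ, the end-of-treatment VAS and SF-36v2, and all follow-up outcomes. A VAS is also taken after the first treatment; its order relative to the blinding items is not given.

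**4. Which way would bias run?**
- If the cue makes guesses more accurate, sham patients may report less benefit and real patients more. Both shifts favour real acupuncture.
- The Background describes the real treatment as causing little pain, shallower than conventional needling and not eliciting qi. Under Real abdominal acupuncture treatment, only CV12 and CV4 reach the superficial muscle; KI17 is needled to 5 mm and ST24 into subcutaneous fat. Some real-arm patients could feel no penetration and conclude they had sham, which would pull the difference the other way.

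The sign is therefore not fixed by the documents.

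**5. Illustration only.** Two inputs are assumed, because the protocol gives neither: an extra 10% to 30% of sham patients conclude they had sham, and this worsens their reported NPQ by 0.2 to 0.5 SD. No shift is assumed in the real arm.

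Bias = share × shift:
- low: 0.10 × 0.2 = 0.02 SD
- high: 0.30 × 0.5 = 0.15 SD

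The protocol's effect size of 0.2, read as Cohen's f for two equal groups, corresponds to d = 2 × 0.2 = 0.4. The bias is then 0.02/0.4 = 5% to 0.15/0.4 = 38% of it.

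Rejection rate of a two-sided 5% t-test with 77 per arm (Sample size determination) and no true effect: noncentrality = bias × √(77/2), 152 degrees of freedom, critical value 1.976.

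| Bias (SD) | Noncentrality | Rejection |
|---|---|---|
| 0.02 | 0.124 | 5.2% |
| 0.05 | 0.310 | 6.1% |
| 0.10 | 0.620 | 9.5% |
| 0.15 | 0.931 | 15.2% |

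The low end is barely distinguishable from the nominal 5%. The table shows what such biases would do; it does not show that they would occur.

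**The case against.** The strongest reply is that the item discloses nothing. It offers three neutral descriptions of sensation to both arms, none is labelled as sham, and the third allows the patient to say they could not tell. That stands in part. A reader might infer that the item tells every patient what the sham is, but the text does not support that: the patient must make the link, and some will not. The item cues; it does not state.

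A reader might also infer that the item breaks the protocol's own rule. The non-disclosure sentence describes what patients are told before randomization, so a later questionnaire does not contradict it. It does undercut the purpose of that sentence.

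The early timing of the item is inferred, as set out above. If only the end was meant, the protocol should say so.

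Other cues also exist. Patients already know that a sham arm exists, are asked to guess after session 1, and are monitored throughout for bruising and bleeding at the points. Looking for marks is possible without this question, and how much the item adds is unknown. What distinguishes it is that it names the specific feature that separates the arms.

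Finally, the item comes from a cited trial. Prior use does not settle the matter here, because withholding the nature of the sham is this protocol's own choice.

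**Conclusion.** The point holds as a risk to the blind. On its natural reading, the plan shows patients the sham's defining feature after session 1, before five more sessions and the post-treatment outcomes, although it deliberately withholds that feature at consent.

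The size of any bias cannot be derived from the documents. The 0.02 to 0.15 SD range and the 5.2% to 15.2% rejection rates rest on two assumed inputs and on a shift in the sham arm alone. A reader might take them as evidence that the trial is biased toward real acupuncture, but the protocol supports neither the magnitude nor a certain direction.

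I would class this as a cheap improvement worth making before enrolment, with moderate confidence, and not as a flaw that must be repaired for the trial to be valid. The sample size is unaffected. Later analysis could not restore a blind weakened in this way, so the remedy belongs in the questionnaire schedule.

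**What to change.** Amend the blinding paragraph under Other measures, and the Table 1 blinding row with its footnote, as follows:

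- After the first treatment, ask only the real/sham guess. It reveals nothing beyond what consent already gives.
- At the end-of-intervention visit, ask the needle-sensation item once, as the last item, after NPQ, VAS, SF-36v2, credibility, satisfaction and the guess.
- Split the Table 1 row in two, so that the dagger stays on the guess (and on VAS) but not on the sensation item.

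This protects the primary endpoint. The 4-week outcomes would still follow the item. Asking it last at the 4-week visit instead would protect them too, at the price of asking patients to recall how insertion felt some weeks earlier; that step is optional.

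The cost is a wording change and a re-ordered form. The early sensation answer is lost; the early guess is kept.
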